## 2.3 Group of patients screened and treated at 5 years of age

|                                                                                                                        | Evaluation
at 5 years +/- 2 months |
|------------------------------------------------------------------------------------------------------------------------|---------------------------------------|
| Oral information and provision of information leaflet and informed consent form                                        | X                                     |
| Signature of informed consent                                                                                          | X                                     |
| Patient's characteristics                                                                                              | X                                     |
| INSEE socio-professional categories                                                                                    | X                                     |
| Childcare, Education, Bilingualism                                                                                     | X                                     |
| Associated rehabilitation (speech therapy, physiotherapy, psychomotricity, palatal plate)                              | X                                     |
| Family history (number of brothers and sisters - patient's rank in the sibling)                                        | X                                     |
| Clinical examination                                                                                                   | X                                     |
| Oral and phonatory apparatus                                                                                           | X                                     |
| Audiometry and ophthalmic examination                                                                                  | X                                     |
| Digestive symptoms                                                                                                     | X                                     |
| Blood test results, if available                                                                                       | X                                     |
| Medical and surgical treatments for OSA                                                                                | X                                     |
| Griffiths III, VABS-II, BRIEF-P and CBCL-P complete, Naming and Word Comprehension (WPPSI-IV), semantic verbal fluency | X                                     |
| PSG as part of care                                                                                                    | X                                     |
| Questionnaire on children's sleep habits                                                                               | X                                     |
| PSQI and Epworth scale for parents                                                                                     | X                                     |
| Adverse events related to ENT, neurological and cardiopulmonary systems                                                | X                                     |

### **3. INTRODUCTION**

#### **3.1 Context and current scientific knowledge**

Obstructive sleep apnoea (OSA) is very common in Down syndrome (DS), affecting around 30-50% of children and 90% of adults. In addition, OSA is more severe in DS patients than in non-DS populations. Risk factors contributing to OSA in DS include midface hypoplasia, relative macroglossia and low muscle tone with pharyngo-laryngomalacia. There is also an increased frequency of lingual tonsillar hypertrophy (10 times more frequent in the DS population), subglottic and tracheal stenosis, obesity (twice as frequent in the DS population), gastro-oesophageal reflux and hypothyroidism, the presence of which may promote or aggravate possible OSA.

The deleterious effects of OSA on neurocognitive development and behaviour are well known. These clearly contribute to the intellectual and motor deficits in DS, even in cases of moderate OSA. Indeed, DS children who snore habitually behave less well at school than DS children who do not snore. DS children with documented OSA show a lower verbal intelligence quotient and cognitive flexibility than DS children without OSA. DS patients also have an increased risk of developing Alzheimer's disease after the age of 35, and the incidence of this degenerative disease is as high as 75% in DS adults. OSA is associated with a reduction in slow wave activity, leading to dysfunction of the prefrontal cortex and an accelerated decline in cognitive function, particularly in the DS population. Indeed, DS patients have a diminished global neuroprotective system, which explains their increased susceptibility to any neurological stress, including OSA.

Screening for OSA is an essential element in the diagnosis and treatment of OSA. But screening is a real challenge. Clinical symptoms are insufficiently sensitive and specific. Nocturnal oximetry lacks sensitivity. The only reliable test is polysomnography (PSG), which enables respiratory events to be detected and quantified, and sleep architecture and quality to be analysed using sleep stages and nocturnal gasometry (with measurement of pulse oximetry (SpO2) and carbon dioxide (CO2)). However, access to PSG is limited because few centres are able to carry out this examination, particularly for younger children. PSG requires specialised equipment and an experienced team, and is a long, difficult and expensive examination that cannot be carried out routinely. International recommendations advise screening for OSA via sleep study in DS children from the age of 4. But we know that OSA can be present from the very first months of life and that its neurocognitive side-effects are all the more significant the younger the child. The first months and years of life are therefore a period of great susceptibility to neurological stress, including OSA. It therefore seems necessary to propose earlier systematic screening in order to treat even moderate OSA in time, in order to prevent or limit the deleterious neurocognitive and behavioural effects of OSA in a population at high neurological risk.

### **3.2 Scientific hypothesis**

Our hypothesis is that OSA is very common, under-diagnosed and therefore under-treated in DS infants, and that systematic screening and optimal correction of OSA during the first 3 years of life is associated with better neurocognitive and behavioural development at 3 years of age.

### **3.3 Clinical experience**

Our sleep and non-invasive ventilation (NIV) unit cares for many newborns and infants with DS. If the sleep study reveals OSA, we adopt a "perfectionist" therapeutic attitude, which aims to completely normalise the sleep disorders observed. Depending on the case, this treatment involves ENT surgery and/or treatment with continuous positive airway pressure (CPAP) in the most severe cases. CPAP involves the delivery of continuous positive airway pressure using a CPAP machine and a mask that is held to the child's face by a small harness or cap. In the case of infants, a nasal mask is used. This CPAP treatment is only used during sleep (at night and during naps) because it is during sleep that airway obstruction is at its greatest. This CPAP treatment can be carried out at home, regardless of the child's age, after the child has adapted and the parents or care giver have received therapeutic training. This CPAP treatment is continued until sleep is completely normalised.

In our clinical experience, we found that infants who were effectively treated with CPAP for OSA from an early age had better neurocognitive and behavioural development than children of the same age who were not screened for OSA. We therefore wish to verify our hypothesis, which is that OSA is very common, under-diagnosed and therefore under-treated in DS infants, and that systematic screening and optimal correction of OSA during the first 3 years of life is associated with better neurocognitive and behavioural development at 3 years of age.

## **4. STUDY OBJECTIVES AND ENDPOINT CRITERIA**

### **4.1 Main objective**

Demonstrate that early (from the age of 6 months), systematic and regular (every 6 months) screening by PSG for OSA (and its treatment if necessary) in a DS population during the first 3 years of life is associated with better neurocognitive development at the age of 3 years compared with a control population not screened by regular PSG.

## **4.2 Secondary objectives**

- Demonstrate that early (from the age of 6 months), systematic and regular (every 6 months) screening by a PSG for OSA (and its treatment if necessary) in a DS population is associated with better behaviour at the age of 3 years compared with a control population not systematically screened.
- Show that OSA is less frequent and less severe at the age of 3 years in DS children screened for OSA (from the age of 6 months) by regular PSG compared with a control DS population with standard care.
- Identify simple objective parameters that could be an alternative to PSG for screening DS children for OSA: pulse oximetry  $\pm$  PtcCO2  $\pm$  suprasternal pressure sensor  $\pm$  actigraphy.
- Evaluate the subjective quality of sleep of the child and their parents during each PSG using questionnaires and correlate these results with the PSG data.
- Demonstrate that, at the age of 5 years, children with DS and with early diagnosed and treated OSA (before the age of 3 years) would have better cognitive development, particularly in terms of language, than those detected and treated late (at the age of 3 years).

## **4.3 Primary endpoint**

To demonstrate that screening for OSA by PSG and its treatment if necessary is associated with an improvement in neurocognitive development; the mean total score and sub-scores of the Griffiths III at the age of 3 years will be compared between the groups.

## **4.4 Secondary endpoints**

- To demonstrate that screening for OSA by PSG and its treatment if necessary is associated with improved behaviour; the mean total scores and sub-scores of the Vineland Adaptive Behaviour Scales, Second Edition (VABS-II), Behaviour Rating Inventory of Executive Function – Preschool (BRIEF-P) and Child Behaviour Checklist - Preschool (CBCL-P) at the age of 3 years will be compared between the groups.
- To show that OSA is less frequent and less severe in the screened children; the number of children with OSA at the age of 3 years and the mean apnoea-hypopnoea index (AHI) at the age of 3 will be compared between the 2 groups;
- To show the value of peripheral saturation,  $\pm$  nocturnal transcutaneous carbon dioxide,  $\pm$  actigraphy,  $\pm$  suprasternal pressure sensor in predicting the presence of OSA with PSG.

- Parents' subjective sleep quality assessed using the Pittsburgh Sleep Quality Index (PSQI) and the Epworth Sleepiness Scale, and the child's subjective sleep quality assessed using the Children Sleep Habits Sleep Questionnaire;
- Assessment of language at 5 years, by analysis of the Quotient of Development for the Language subscale (QDL) of the Griffiths III, by analysis of the raw scores of the Naming and Word Comprehension tests of the Wechsler Preschool and Primary Scale of Intelligence - Fourth Edition (WPPSI-IV), a verbal fluency task (number of words produced in one minute) and by the CBCL-P language proxy questionnaire (number of words produced in French and a foreign language).
- Assessment of cognitive functions, by analysing the Composite Global Executive (CGE) Score and scores on the Inhibitory Control, Flexibility and Emerging Metacognition Indices, as well as the scores of the different sub-domains within each index obtained from the BRIEF-P scale;
- Assessment of behaviour by analysing the mean total scores and sub-scores obtained on the CBCL-P proxy questionnaire and the VABS-II.
- Finally, the results obtained from the Griffiths III, the BRIEF-P and CBCL-P proxy questionnaires and the VABS-II at 5 years will be compared with the results obtained at 3 years.

As the language proxy questionnaires was not offered to the parents of children aged 3 years, given the limitations of verbal expression in patients with DS, the analysis will focus solely on the results obtained at age 5 years and on the comparison of these results between the two groups at age 5 years.

## **5. POPULATION ELIGIBILITY CRITERIA**

### **5.1 Inclusion criteria**

- Child aged 0 to 6 months (*Screened Group*) or  $36 \pm 1$  months (*Standard Care Group*) at the time of inclusion
- Child with DS (genetically confirmed with a karyotype showing free and complete trisomy 21 or Robertsonian and homogeneous translocation [mosaic excluded])
- Child with no other pathologies such as:
  - neurological and/or degenerative pathology (West syndrome, etc.)
  - pathology at high risk of OSA: pathological facial malformations, achondroplasia, mucopolysaccharidosis, Prader Willi, etc.
  - anoxo-ischaemic encephalopathy requiring treatment with hypothermia
  - associated leukaemia
  - uncontrolled heart rhythm disturbances
- Living in Paris or the inner suburbs: departments 75, 77, 78, 91, 92, 93, 94, 95.
- French language predominant in the living environment

- Child who can reasonably be expected to attend the consultations scheduled as part of the study, to be able to take the planned tests according to the investigator, in particular the Griffiths test (e.g., absence of hearing or visual problem)
- Child whose parents or legal representative can be reached by telephone
- Parents or legal representatives who accept the constraints of the study and are able to understand, date and sign the informed consent form (ICF) before the patient is enrolled in the study
- Child beneficiary of a social security system

### **5.2 Non-inclusion criteria**

- Child with a gestational age < 36 completed weeks of amenorrhoea
- Child presenting or having presented signs of acute central nervous system distress: Stroke, post-operative hypoxia, meningitis
- Child with DS already treated with CPAP for OSA
- Child participating in other interventional research involving humans or for whom participation in other interventional research involving humans is planned during the study duration
- Child whose parents do not understand the constraints related to the study
- Child whose parents plan to move outside the Paris region before the end of the study.

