| POPULATION | 
80 patients from 2 populations: the Screened Group (40 patients) and the Standard Care Group (40 patients, control group).
 
 
• The infants in the Screened Group are children who are seen at the IJL every year and who receive PSG at home every <math>6 \pm 1</math> months from the age of 6 months until the age of 3 years. At the age of 3 years, the children will have a final PSG with a cognitive and behavioural assessment.
 
• Children in the Standard Care Group are children who are seen at the IJL at the age of 3 as part of their usual follow-up. These children will have a single PSG, a medical assessment, and a neurocognitive and behavioural assessment at the age of 3 years, which will be used as a reference in relation to the Screened Group. These children will not be monitored prospectively, and information concerning their medical follow-up before the age of 3 years will be collected from their medical records.
 
 
If the children in the Screened Group are diagnosed as having OSA, they will receive appropriate treatment using the local practice in [name] unit at the Necker-Enfants Malades Hospital.
 
For patients in the Standard Care Group who will have benefited from PSG and appropriate treatment of their OSA before their 3rd birthday, the corresponding data will be collected from their medical records at their 3rd birthday visit to the Institut Jérôme Lejeune.
 |

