All these treatments will be carried out at the Necker-Enfants Malades Hospital. A follow-up PSG will be performed to check that the sleep disorders have been corrected. This control PSG will be either a systematic PSG scheduled as part of the study, or an additional PSG for medical reasons. Other visits and/or hospitalisations may be necessary for medical reasons. In all cases, the schedule of one PSG every 6 months must be complied with.

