#### 7.3.1 Visit V0: inclusion

Before any examination, the patient's legal representatives will sign the ICF and the patient's eligibility will be confirmed. Parents (legal representatives) will be asked to bring their child's karyotype results to the visit. The following data will be collected:

- Patient's characteristics at birth

- Timing of DS diagnosis: pre- or post-natal and karyotype result
- Gestational age, birth weight, height and head circumference
- Medical history and associated pathologies
- Malformations
- Associated sensory deficits: deafness, blindness
- Clinical examination: weight, height, head circumference
- Residence and childcare
- Digestive symptoms
- Rehabilitation
- Blood test results if available (TSH, haemogram)

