### 7.3.9 V3 end-of-study visit at 36 ± 1 months

- Clinical examination
- Documentation of psychomotor development
- Digestive symptoms
- ENT follow-up
- Ophthalmic follow-up
- Blood test results if available (TSH, haemogram)
- Rehabilitation
- Investigator's judgment of sleep apnoea
- Apnoea observed by parents
- Childcare arrangements
- Acquisition of toilet training skills at night yes/no
- Acquisition of toilet training skills during the day yes/no
- Neuropsychological tests: Griffiths III, VABS-II, BRIEF-P, CBCL-P
- Medical and surgical treatments
- AEs

For children in the *Standard Care Group*, this visit will be combined with the inclusion visit.

Signature of the informed consent by the legal representatives for the 5-year follow-up within 15 days of the 3-year visit.

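### Health-related eligibility is judged at 0-6 months in the Screened Group but at 36 months in the Standard Care Group, so the controls are a filtered version of standard care

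*Protocol*

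**What the plan says.** Protocol 5.1 sets age at inclusion as "Child aged 0 to 6 months (*Screened Group*) or" 36 ± 1 months for the Standard Care Group. All other criteria in 5.1 and 5.2 are common to both groups, and none is tied to a reference age. At V0 (7.3.1) "the patient's eligibility will be confirmed". For Standard Care children, 7.3.9 states of the 3-year outcome visit that "this visit will be combined with the inclusion visit". Their eligibility is thus settled at the visit where the outcome is measured.

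Section 5.2 excludes a "Child with DS already treated with CPAP for OSA", and any child with a past or present stroke, post-operative hypoxia or meningitis. Section 5.1 excludes neurological disease such as West syndrome, leukaemia and uncontrolled arrhythmia, and requires the child "to be able to take the planned tests according to the investigator, in particular the Griffiths test".

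The Synopsis (Population) says that for Standard Care children "who will have benefited from PSG and appropriate treatment of their OSA before their 3rd birthday, the corresponding data will be collected" from their records. Sections 7.1 and 7.3 say much the same. In 9.3, ITT means included children with a primary endpoint assessment. The per-protocol set excludes major deviations, and the presence of an exclusion criterion is one of the examples given, with no age attached.

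**The concern.** In a non-randomised comparison of two age cohorts, comparability depends on both groups passing the same filter at the same point in life. Here the controls pass through about 30-36 months more of it. A control who starts CPAP, has meningitis or develops leukaemia at age 2 is never enrolled. A Screened child with that history was already included. CPAP is part of the care being tested (6.1), and later onset of an exclusion criterion is not itself a listed reason for withdrawal (7.3.14).

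The protocol regards such events as relevant: section 8.1 says neurological events are monitored because they confound intellectual disability and may influence the primary endpoint. They are filtered from one group up to the day of testing and retained in the other. The comparator named in 4.2 is a Down syndrome population under standard care; what is enrolled is the part of it that reached age 3 without these events. The regression in 9.3.1 adjusts among enrolled children only.

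**Working it through.** **1. The plan's own figure.** Inputs from 9.1 and 9.3: difference 8 points, SD 11.55, two-sided 5%, power 80%.
- Normal approximation: n = 2(1.960 + 0.842)² × (11.55/8)² = 2 × 7.849 × 2.084 = 32.7, so 33 per group.
- Exact two-sample t-test: 34 per group, power 80.3%.
- Attrition: 34/0.85 = 40 per group.

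The stated 34 and 40 reproduce. There is no arithmetic error; the calculation simply makes no allowance for selection of controls.

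**2. Which criteria depend on age at inclusion.** Karyotype, gestational age and neonatal encephalopathy are settled at or near birth and do not differ between groups. These do:

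| Criterion | Window, Screened | Window, Standard Care | Screened child with later onset |
|---|---|---|---|
| CPAP for OSA | to 6 months at most | to about 36 months | stays in |
| Stroke, post-operative hypoxia, meningitis | to 6 months at most | to about 36 months | stays in |
| West syndrome, leukaemia, uncontrolled arrhythmia | to 6 months at most | to about 36 months | stays in |
| Able to take the Griffiths (hearing, vision) | forecast in infancy | observed at 36 months | leaves ITT if not assessed |

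The last row is partly offset by the ITT definition. The first three are not, provided the Screened child attends and is tested.

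**3. Size (assumptions).** Let f be the fraction of standard-care children removed by the later filter and g the difference between their mean and that of the retained children. The full standard-care mean is then the retained mean + f·g, so filtering shifts the control mean by −f·g. The documents give neither f nor g. With SD 11.55, 34 per group and a true effect of 8 points:

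| f | g | Shift in control mean | Expected difference | Power | Rejection rate if no true effect |
|---|---|---|---|---|---|
| 5% | −10 | +0.5 | 7.5 | 75% | 5.4% |
| 10% | −10 | +1.0 | 7.0 | 69% | 6.4% |
| 15% | −15 | +2.25 | 5.75 | 52.5% | 12.4% |
| 20% | −15 | +3.0 | 5.0 | 42% | 18.4% |
| 5% | +5 | −0.25 | 8.25 | 83% | 5.1% |
| 10% | +10 | −1.0 | 9.0 | 89% | 6.4% |
| 15% | +10 | −1.5 | 9.5 | 92% | 8.2% |

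For 5-15% removed and 10-15 points lower, the shift is 0.05 × 10 = 0.5 to 0.15 × 15 = 2.25 points, or 0.5/8 = 6% to 2.25/8 = 28% of the target. The 20% row is an outer case.

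**4. Direction.** Removing children with neurological or serious illness most plausibly raises the control mean and works against the trial's hypothesis. Removing CPAP-treated controls could do the same, if they are the most severe cases, or the reverse, if CPAP helped them. The two can cancel: 10% at −10 and 10% at +10 give +1.0 − 1.0 = 0.

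**The case against.** The strongest case against is that the numbers are invented: no passage gives the share removed, their scores or the direction. That stands. It limits what can be said about size, but not the timing gap, which follows from 5.1, 5.2, 7.3.1 and 7.3.9 alone.

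It is also fair that ability to be tested is not a one-sided filter, since untestable Screened children leave the ITT set too. The offset is only partial: a Screened child with a hearing or visual problem who can still be assessed stays in, whereas a control with the same problem may be refused.

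Two stronger readings are tempting.
- *A reader might infer that the CPAP criterion flatly contradicts the Population text.* It does not. OSA treatment in 6.1 includes adenoidectomy and tonsillectomy, so ENT-treated controls satisfy both passages. What remains is unclear scope: the Population text does not say that CPAP-treated children fall outside it, and 5.2 does not say whether CPAP that has been stopped counts.
- *A reader might infer that the 3-year OSA comparison is an artefact*, because 6.1 says "A follow-up PSG will be performed to check that the sleep disorders have been corrected" and lets a scheduled PSG serve that purpose, so that a Screened child controlled on CPAP would count as OSA-free. No passage says the 36-month PSG is recorded on CPAP or how such a child is classified. That rule may properly sit in the statistical analysis plan, which is not at hand.

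Finally, on the Synopsis calendar inclusion ran from June 2017 to June 2019, so new wording may come too late to recover excluded controls. This affects which remedy is feasible, not whether the problem exists.

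**Conclusion.** The concern holds in this form: time-varying health criteria (CPAP for OSA, acute CNS events, neurological pathology, leukaemia, uncontrolled arrhythmia) are applied about 30-36 months later in controls, who are therefore a selected part of standard care. This much rests on the text and needs no assumption.

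Size and direction cannot be determined from the documents. Under the stated assumption (5-15% removed, 10-15 points lower) the control mean is inflated by 0.5-2.3 points and power falls from 80% to between 75% and 52.5%. If the removed children would have scored higher, the expected difference is inflated instead. An unknown sign makes both a positive and a null result harder to read, and the planned t-test and regression cannot resolve it.

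A related ambiguity sits in 9.3. If the exclusion-criterion deviation were judged at 36 months, the per-protocol set would lose Screened children who received CPAP under the strategy being tested.

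**What to change.** 1. **Common reference age.** State that the time-varying health criteria are judged by status at 6 months in both groups, using for controls the medical records already being collected. Reconcile the scope of the CPAP criterion in 5.2 with the Synopsis, 7.1 and 7.3, which expect controls treated for OSA before age 3, and say whether past CPAP counts.
2. **Per-protocol rule.** In 9.3, state that the presence of an exclusion criterion is judged at inclusion.
3. **If control inclusion is closed.** Add a sensitivity analysis of the primary endpoint that applies the 36-month health criteria, other than CPAP, to the Screened Group. Neurological and cardiopulmonary events are already recorded (8.2). Leukaemia lies outside those categories but should be traceable from the treatments recorded at visits and two-monthly calls. Report how many control candidates were excluded at 36 months and why, where known.

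Cost: amendment wording and one extra analysis, with no added visit or procedure. Some control history would rest on records of uneven quality, and the sensitivity analysis would lose a few Screened children.
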